### Hypotheses

The present study aims to investigate whether the enhanced implementation of BEs will improve the efficacy of CT for SAD. This goal will be achieved by the following measures:
comprehensive training of the therapists’ competencies in conducting in-session BEs, including self-practice and self-reflection,encouraging therapists to implement this intervention as the major component of the treatment in continuous supervision,establishing double hour sessions to ensure an appropriate setting for BEs.

The experimental condition (CT plus enhanced BEs) will be compared to standard CT as the control condition. An active control condition has been chosen as comparator to control for specific effects of conventional components of cognitive therapy. In standard CT, therapists’ training, supervision, and settings are arranged with a focus on traditional cognitive restructuring techniques.

In a randomized controlled trial, the following major hypothesis will be tested:*Hypothesis 1: As compared to standard CT, CT plus enhanced BEs will result in a significantly higher rate of responders at (a) post-treatment and (b) follow-up.*

The secondary objective is to identify differences in the process of therapy and their association with treatment outcomes. The process-related variables to be assessed include the following therapist variables: general and treatment-specific competencies, and adherence to and allegiance with the treatment manual. The patient variables and treatment outcomes are: changes in insight in SAD-related beliefs, cognitions, avoidance, and symptoms, as well as comorbid depressive symptoms.*Hypothesis 2: In the CT plus enhanced BEs, as compared to standard CT, therapists will show higher levels of adherence related to BEs, and significantly higher levels of allegiance with the treatment approach.**Hypothesis 3: In CT plus enhanced BEs, as compared to standard CT, changes in SAD-related insights, cognitions, avoidance, and symptoms (a) from baseline to post-treatment, and (b) from baseline to follow-up will be significantly increased.*

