An additional objective is to identify outcome predictors, including therapist and patients’ variables and the therapeutic relationship.*Hypothesis 4:**The following variables are expected to predict positive treatment outcomes:**Therapist variables: competencies, adherence, and allegiance; therapist-rated therapeutic relationship**Patient variables: preferred learning style at pre-treatment, changes in insights in SAD-related beliefs, changes in SAD-related cognitions; patient-rated therapeutic relationship.*

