**Fig. 1 Fig1:**
[figure not shown]
Study flowchart. Flowchart of planned participants’ selection and study design

The study is designed to detect a moderate effect size (d = 0.60, f = 0.35), as observed in the meta-analysis for CT for SAD with intense BE and prolonged sessions, as compared to CT with a reduced number of BEs and shortened sessions [7]. A power analysis with 90% power on a two-sided test where α = 0.05 revealed a sample size of *N* = 54 (27 per group). Based on data from previous studies [5], we expect a drop-out rate of 10%. Thus, 60 patients (30 per group) will have to be recruited.

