### Statistical Analyses

Data will be analyzed with the SPSS statistical software package. All statistical analyses will be conducted on the intent-to-treat (ITT) sample and completer sample. Patients allocated to treatments will be classified as drop-outs if they miss more than 25% of the sessions. In the ITT analyses of treatment response, drop-outs will be considered as failures. In ITT analyses of dimensional measures, missing data will be replaced using the last observation carried forward approach for missing intervention- and post-assessments or follow-up observations. Analyses of the primary outcome measure (CGI-I), a categorical variable, will be conducted using χ^2^ or Fisher's exact tests. Dimensional measures will be submitted to analyses of covariance (ANCOVAs) in which pre-treatment scores will be controlled for. ANCOVAS will be performed separately for the post-treatment and 6-month follow-up assessments. Significance levels will be set at *p* < 0.05, two-tailed. Predictor analysis will be calculated by using logistic regression analysis with CGI-I as the dependent variable; independent variables are competencies, adherence, allegiance, and therapist-rated therapeutic relationships (therapist predictors), as well as patients’ preferred learning style at pre-treatment, changes in insight in SAD-related beliefs and cognitions, and patient-rated therapeutic relationships (patient predictors). Differences between treatments in the outcome predictions will be analyzed, with treatment interactions for each predictor. To test for possible therapist differences, a preliminary analysis of covariance will be conducted. As recommended, significance level in this case will be set at *p* < .30 [37]. If the effect is significant, a multilevel analysis using a mixed-model design is planned to include therapists as a random term [38]. A final analysis will be run to compare the pattern of results from both strategies of analysis taking possible therapist effects into consideration.

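### Hypothesis 4 tests at least 16 predictor and interaction terms at an unadjusted p < 0.05 in 54–60 patients; if nothing predicts response, at least one is significant in roughly 40–65% of trials

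*Protocol article*

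**What the plan says.** The Hypotheses section sets Hypothesis 4 under an additional objective: "The following variables are expected to predict positive treatment outcomes", followed by a list of therapist and patient variables. The Statistical Analyses section turns this into a model: "Predictor analysis will be calculated by using logistic regression analysis with CGI-I as the dependent variable". The therapist side is "independent variables are competencies, adherence, allegiance, and therapist-rated therapeutic relationships (therapist predictors"; the patient side is "preferred learning style at pre-treatment, changes in insight in SAD-related beliefs and cognitions, and patient-rated therapeutic relationships (patient predictors". Interactions follow: "Differences between treatments in the outcome predictions will be analyzed, with treatment interactions for each predictor".

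The level is given in the sentence just before the predictor analysis: "Significance levels will be set at *p* < 0.05, two-tailed". The same section names a different level, 0.30, for the preliminary check on therapist differences, so it states an exception where one is meant. It states none for the predictors.

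On size, Design and Sample Size gives 54 evaluable patients and then: "Thus, 60 patients (30 per group) will have to be recruited". The text does not say whether the eight predictors enter one model or several, nor whether the interactions enter together.

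**The concern.** Sixteen or more tests, each at 5%, in about 60 patients will often produce at least one small p-value by chance. Hypothesis 4 does not say how many variables must be significant, or which, before it counts as supported. A report could therefore single out whichever term crosses 0.05. The abstract presents the results as relevant to clinical training, so a chance finding for competence, adherence or allegiance could influence how therapists are trained. The interactions are not incidental either: Additional Assessments predicts that different learning styles matter in the two arms, which is a predictor-by-treatment claim.

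A second problem arises only if all terms enter one regression: the model would then be too large for the data.

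**Working it through.** **The plan's own figure.** The article gives no error rate for the predictor analysis, so there is none to reproduce. The patient numbers used here are 54 and 54/0.9 = 60; how 54 was reached is a separate question and does not enter.

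**Count of tests (Statistical Analyses).**
- Therapist predictors: competencies, adherence, allegiance, therapist-rated relationship = 4.
- Patient predictors: learning style, change in insight, change in cognitions, patient-rated relationship = 4.
- Interactions: one per predictor = 8.
- Tests: 8 + 8 = 16. This is a minimum, because the Hypotheses section lists "general and treatment-specific competencies, and adherence to and allegiance with the treatment manual". Splitting competencies in two gives 9 + 9 = 18.

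**Independent tests, nothing predictive.** P(at least one p < 0.05) = 1 − 0.95^k:
- k = 8 (main effects): 33.7%
- k = 16: 56.0%
- k = 18: 60.3%

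**Simulation, because the tests are neither independent nor exact.** The article gives no predictor correlations and no expected response rate, so these are assumptions: eight normal predictors, common correlation 0 to 0.7, response rate 50% or 65%, n = 54 or 60, no true effects, 500 trials per setting (Monte Carlo standard error at most √(0.25/500) = 2.2 points). With separate models, the chance of at least one p < 0.05 was:

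| Correlation | 16 terms, Wald | 16 terms, likelihood ratio | 8 main effects, Wald | 8 main effects, likelihood ratio |
|---|---|---|---|---|
| 0 | 50–53% | 61–62% | 26–29% | 35–36% |
| 0.3 | 48–50% | 58–61% | 27–29% | 34–36% |
| 0.5 | 41–47% | 50–55% | 23–27% | 29–32% |
| 0.7 | 28–38% | 33–45% | 14–20% | 16–24% |

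With one joint 16-term model, Wald tests gave at least one p < 0.05 in 42–63% of all trials, counting failed fits as no finding; 2–18% of fits separated or did not converge. Among converged fits the extremes are 0.418/(1 − 0.164) = 50% and 0.628/(1 − 0.022) = 64%. Likelihood-ratio tests in the joint model gave 75–84%.

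A repeat simulation at correlations 0–0.5 gave 42–55% (separate models), 49–66% of converged joint fits with 1–16% failing, and about 22–35% for the main effects alone.

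**Two analysis sets.** The section runs every analysis on both the ITT and the completer sample. Counting a hit in either set (separate models, Wald), the rate is 67–68% at correlation 0, 57–60% at 0.3, 51–55% at 0.5 and 41–43% at 0.7.

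**Size of a joint model.** Parameters: 16 + treatment + intercept = 18. The smaller outcome class has at most 60/2 = 30 patients, so at most 30/18 = 1.7 per parameter. At an assumed 65% response it is 0.35 × 60 = 21, or 21/18 = 1.2.

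**Effect of adjustment.** At 0.05/16 = 0.0031 per test, 1 − (1 − 0.0031)^16 = 4.9%.

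**The case against.** The strongest reply is that this is a condensed article, that Hypothesis 4 ranks below the primary and secondary objectives, and that model building and multiplicity at that level are commonly left to the analysis plan. That would answer a complaint that detail is missing. It does not answer this one, because the article itself fixes the predictors, the interactions and the 5% level.

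Other objections stand in part:

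- **What Hypothesis 4 names.** It names eight main effects and no any-of-16 success rule. For those eight the chance is about 22–35%, and if each were judged only in one pre-stated direction, 1 − 0.975^8 = 18%. A reader might infer that Hypothesis 4 itself produces a false predictor in most null trials. The documents do not support that: rates near or above one half need the interactions, and a significant interaction is a differential predictor.
- **Correlated predictors.** Adherence and competence are rated on the same tapes, so strong correlation is plausible. At 0.7, separate models give 28–38% by Wald test.
- **The joint model.** A reader might infer that the plan prescribes an 18-parameter regression. It does not say so. The failed fits and the 75–84% figure apply only if all terms are entered together.
- **The global null is a worst case.** The Background cites a correlation of 0.28 between competence in behavioral experiments and outcome. But real effects for some variables do not protect the rest: if four of the 16 terms were real, the other 12 would still give 1 − 0.95^12 = 46% under independence.
- **Strict adjustment costs power.** Firth-penalised Wald tests with Holm adjustment are too conservative here. In null data the first Holm step rejected in 0–0.7% of trials. At a true correlation of 0.28, power for one predictor was about 2–6% with centred treatment coding and about 0% with 0/1 coding.

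**Conclusion.** The point holds in a limited form and should be acted on. The plan tests at least eight predictors and eight interactions at an unadjusted 5% in 54–60 patients. If nothing predicts response, at least one term is significant in roughly 40–55% of trials with separate models at correlations up to 0.5, by Wald test (somewhat more by likelihood ratio, fewer at very strong correlation). In one joint model it is roughly 50–65% of converged fits. For the main effects alone it is about 22–35%. These figures rest on assumed response rates and correlations and on no true effects.

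The overfitting concern is conditional on a joint model. Nothing here touches the primary comparison of responder rates; what is affected is how much a reported predictor or differential predictor can be trusted.

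**What to change.** In Statistical Analyses, replace the predictor text with wording to this effect:

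- Each predictor is fitted in its own logistic model with treatment (coded −0.5 and +0.5), the predictor and their product. Penalised likelihood is used where separation occurs. Centred coding matters because with 0/1 coding and the product in the model, the predictor coefficient describes one arm only.
- Odds ratios are reported with 95% confidence intervals, the number of tests is stated, and the predictor and interaction analysis is labelled exploratory.
- No variable is called a predictor or differential predictor of outcome on an unadjusted p < 0.05 alone.
- If a confirmatory claim is wanted, Holm adjustment is applied across all the tests, using likelihood-ratio p-values from the separate models rather than Firth-Wald p-values. At this sample size those p-values run slightly liberal (61–62% in the table at zero correlation, against 56% expected), so a borderline adjusted result still needs caution.

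The cost is a few sentences and a little programming, with no new data or patients. The downside is that Hypothesis 4 becomes mainly descriptive.

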### Therapists

Therapists are recruited from courses in advanced clinical training for behavioral therapy and are randomly allocated to one of the two conditions. The randomization to either CT plus enhanced BEs or standard CT is uniquely conducted to prevent contamination.

In each condition, training comprises three 8-h days:

In the CT plus enhanced BEs condition, training will focus on the specific competencies to derive, plan, conduct, and analyze BEs.

In the standard CT condition, training will focus on the specific competencies to practice techniques of cognitive restructuring.

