### Randomization

We will use two levels of randomization. Firstly, therapists are randomized to either CT + BEs or Standard CT as described above. Secondly, participants will be randomly assigned to a therapist of one of the two treatment conditions. The random allocation sequence will be generated by a randomization program [19]. Allocation to treatment of the patients is concealed from investigators and patients. The random allocation schedule will be drawn up and administered by a psychologist from another department of the university who is not involved in the further study process. After meeting the inclusion criteria, the participant is allocated by this psychologist to a therapist of one of the treatment conditions. The investigators and therapists are informed about the allocation.

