## Statistical Procedures

### Analysis of Outcome Variables

The primary outcome measure of the study is the proportion of treatment responders at post-treatment rated by the CGI-I. We dichotomize the variable so that treatment responders are defined by a rating of 1 or 2 (markedly or moderately improved from baseline) and non-responders by a rating of 3 or higher [5, 22]. The secondary outcome variables are changes in the mean scores of LSAS and SPIN from baseline to post-treatment. In addition, the primary and secondary outcome variables will be analyzed at 6-month follow-up to examine changes from baseline to follow-up assessment.

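### Therapists are nested within arms, but the primary CGI-I test ignores them, a therapist term depends on a p < .30 screen, and no rule says which analysis decides Hypothesis 1

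*Protocol article*

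**What the plan says.** All references are to the Protocol article.

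- **Design.** Under Therapists: "Therapists are recruited from courses in advanced clinical training for behavioral therapy and are randomly allocated to one of the two conditions". Under Randomization: "Firstly, therapists are randomized to either CT + BEs or Standard CT as described above", after which "participants will be randomly assigned to a therapist of one of the two treatment conditions". Each therapist therefore works in one arm only.
- **Primary outcome.** Under Analysis of Outcome Variables: "The primary outcome measure of the study is the proportion of treatment responders at post-treatment rated by the CGI-I". A rating of 1 or 2 counts as response, so the outcome is binary.
- **Primary test.** Under Statistical Analyses: "Analyses of the primary outcome measure (CGI-I), a categorical variable, will be conducted using" chi-square or Fisher's exact tests. No therapist term is mentioned. The level is fixed there too: "Significance levels will be set at *p* < 0.05, two-tailed".
- **Therapist effects.** The same section plans a preliminary ANCOVA for therapist differences, judged at p < .30. Then: "If the effect is significant, a multilevel analysis using a mixed-model design is planned to include therapists as a random term". It ends: "A final analysis will be run to compare the pattern of results from both strategies of analysis taking possible therapist effects into consideration".
- **Sample size.** Design and Sample Size gives 54 patients, raised to 60 (30 per group) for 10% drop-out. It states no allowance for clustering.

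**The concern.** When each therapist delivers only one treatment, differences between therapists form part of the difference between arms. A test that counts every patient as independent understates the variance of that difference. Three features of the plan leave this unresolved.

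1. The named primary test has no therapist term.
2. The therapist term depends on a screen. The screen is an ANCOVA, which the same section otherwise reserves for dimensional measures; the primary outcome is binary, and nothing says how the screen applies to it.
3. After a positive screen the two sets of results are compared, but neither is named as decisive. If they disagree, Hypothesis 1 has two answers.

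At stake is whether the trial's main test has a defined 5% error rate. The article itself treats therapists as important: its Background reports a correlation of 0.28 between competence in behavioural experiments and outcome in an earlier German trial. That figure is not an ICC, but it makes zero clustering a poor default.

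**Working it through.** **Inputs from the article.** 30 patients per arm (54/(1 - 0.10) = 60, halved); two-sided 0.05; binary response; screen at p < .30.

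**Assumptions, not in the article.** k = 3, 5, 6 or 10 therapists per arm with equal caseloads m = 30/k, and 15 per arm as a further case; latent ICC 0.05 or 0.10; the same true response rate in both arms (50% for the approximation below).

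**Step 1. Reproduce the nominal level.** With ICC 0, simulated chi-square type I error is 4.7-5.3%, in line with the stated 5%. Fisher gives about 2.6%, reflecting its usual conservatism.

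**Step 2. Put the ICC on the response scale.** For a probit latent variable and 50% response, response ICC = (2/π) × arcsin(latent ICC). Latent 0.05 gives 0.032; latent 0.10 gives 0.064.

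**Step 3. Approximate the chi-square error.** Design effect DE = 1 + (m - 1) × response ICC; error = 2 × [1 - Φ(1.96/√DE)].

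Example with 5 therapists per arm and latent ICC 0.10: DE = 1 + 5 × 0.064 = 1.32; 1.96/√1.32 = 1.71; error = 8.8%.

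| Therapists per arm × patients each | Latent ICC 0.05: formula | Simulated | Latent ICC 0.10: formula | Simulated |
|---|---|---|---|---|
| 3 × 10 | 8.4% | 8.6% | 11.8% | 12.6% |
| 5 × 6 | 6.9% | 6.9% | 8.8% | 9.0% |
| 6 × 5 | 6.5% | 7.0% | 8.0% | 8.0% |
| 10 × 3 | 5.7% | 6.0% | 6.5% | 6.6% |
| 15 × 2 | 5.4% | - | 5.7% | - |

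The simulated columns are null simulations with 20,000 replicates per cell. Formula and simulation agree closely.

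**Step 4. The other routes, for 3 to 10 therapists per arm.**

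- Fisher's exact test: about 3-8%.
- Screen at p < .30, taken as an F-test of therapist within arm on the 0/1 response: negative in roughly 40-60% of trials although clustering is real.
- Mixed model strictly replacing chi-square after a positive screen (represented by its balanced-design equivalent, a therapist-level t-test): about 4-6%.
- Therapist-level t-test in every trial, no screen: 4.6-5.4%.

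**Step 5. Sensitivity to the ICC scale.** If 0.05 and 0.10 are read as response-scale ICCs (50% response), chi-square error is 8.2% and 11.5% with 5 therapists per arm, 10.9% and 16.1% with 3, and 6.0% and 6.4% with 15. Any ICC used for planning should therefore name its scale.

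**The case against.** The plan does not overlook therapists. It sets a deliberately liberal screen and plans a multilevel model when that screen is positive. On the natural reading, the multilevel result then replaces the simple test, and the error stays at about 4-6%, or lower with Fisher as the fallback. Fisher alone is often below 5%. With many therapists the whole matter is small. The article is also a condensed account, and small-sample details may sit in a plan that is not shown.

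Much of this stands. A reader might infer that the planned procedure as a whole has been shown to inflate the type I error. The document does not support that: the result depends on which analysis decides, which test is used and how many therapists there are, and the departure can be downward. A reader might also infer that success on either analysis would count. The article says no such thing. Under its gate, that rule would in any case add nothing to chi-square alone, because the mixed model runs only when therapist variation looks large.

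Three further inferences do not hold:

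- **Too narrow a confidence interval.** The article specifies none for the primary outcome.
- **Allegiance mistaken for a treatment effect.** Raising allegiance is part of the intended intervention (Hypothesis 2), and a therapist random intercept would not remove a systematic difference between arms.
- **Missing baseline adjustment.** CGI-I already rates change from baseline, and an unadjusted randomised comparison is valid.

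What the objection does not answer is the missing decision rule. The replacement reading is not written down; the article says only that the patterns of results will be compared. Nor is this merely a detail deferred to another document, since the article itself fixes the test, the screen, the threshold and the comparison.

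**Conclusion.** The concern holds as a defect in how the primary analysis is fixed: the named test ignores a nesting that the randomisation creates, the correction depends on a screen ill-suited to a binary outcome, and no rule says which result decides. The error rate for Hypothesis 1 is therefore undefined.

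If chi-square decides, it is about 6-13% under the assumptions above: about 7-9% with 5 therapists per arm, and only slightly above 5% with 15. If Fisher decides, it is about 3-8%. Under strict replacement it would be about 4-6%.

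The structural finding rests on the text alone. The size rests on an assumed number of therapists, ICC and equal caseloads, none of which the article gives, and should be read as a range.

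**What to change.** 1. Drop the p < .30 screen.
2. Name one decisive analysis of CGI-I response that always accounts for therapist. Two candidates are a t-test on therapist-level response proportions, and a mixed logistic model with a therapist random intercept and small-sample degrees of freedom. Choose in advance, not by whether a model converges, since that would be another data-dependent switch. Only the therapist-level test was checked here (4.6-5.4% with equal caseloads); the mixed logistic model should be checked by simulation for the actual caseloads before it is chosen.
3. Include a therapist random intercept in the models for the dimensional measures.
4. Report the unclustered chi-square or Fisher test as descriptive or sensitivity only.
5. State the planned number of therapists and a response-scale ICC, and restate power with them. For example, 5 therapists per arm and a response-scale ICC of 0.064 give DE = 1.32, so 30 patients per arm carry the information of about 30/1.32 = 23.

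The cost is in wording and precision, not in data collection. A therapist-level test has 2(k - 1) degrees of freedom: 8 with 5 therapists per arm (critical t 2.31 against 1.96) and 4 with 3 per arm (2.78). Nominal power falls accordingly, which makes the number of therapists a planning choice worth stating.
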